### IIb. stroke unit care

The patient will be admitted to a stroke unit or medium care unit and is treated according to local practice, supplemented with the treatment options that can be performed in a medium care unit as described above under 'a'.

Treatment strategy 'I' is the experimental option, strategy 'IIa' is recommended by international experts, and strategy 'IIb' is the most common clinical practice in the Netherlands, and probably also in a significant number of other European countries.

The choice of ancillary care measures, e.g., prophylactic administration of (low-molecular-weight) heparin and the treatment of complicating illnesses, will be at the discretion of the treating physician. However, administration of low-dose aspirin is recommended, whereas treatment with intravenous heparin and haemodilution with plasma expanders are discouraged.

### Outcome assessment

The primary outcome measure will be functional outcome, as determined by the score on the mRS, at one year. Outcome will be dichotomised as 'good' (mRS 0 to 3) or poor (mRS 4 to dead). The score on the mRS will be determined in a standard way independently by three blinded investigators, on the basis of a narrative written by an unblinded independent study nurse, if necessary followed by a consensus meeting. Secondary analyses will be performed in which 'good outcome' will be defined as mRS 0 to 2, and 'poor outcome' as mRS 3 to dead, and with case fatality as the measure of outcome. Other outcome measures will include the scores on the NIHSS, the BI, and the Montgomery and Asberg Depression Rating Scale (MADRS) [32] and quality of life as measured with the SF3633 and with a visual analogue scale (VAS) [33] at one year and at three years. In addition, the mRS, NIHSS, and BI will be determined at 3 and 6 months.

### Data collection

At baseline, the medical history will be assessed and a general and neurological examination will be carried out. The scores on the GCS and NIHSS will be used to assess stroke severity on admission and directly prior to randomisation. Retrospective scoring of the NIHSS on admission is reliable when a published algorithm is used [34]. Date and time of stroke onset and of neurological deterioration (i.e. GCS ≤ 13) will be noted. Laboratory investigations will include a blood cell count, electrolytes, serum glucose, creatinine, and liver enzymes. Brain CT or MRI scans will be performed on admission and prior to randomisation. Lateral displacement of the pineal gland and the septum pellucidum will be measured by the trial co-ordinator.

The GCS, pupillary reflexes, body temperature, and blood pressure will be assessed every 4 hours during the first 4 days after randomisation. If ICP is recorded, ICP and cerebral perfusion pressure (CPP) will be noted at 2-hour intervals. Dose and time of administration of osmotic agents and sedatives, concurrent medication, and neurological and systemic adverse events will be recorded. The GCS, NIHSS, mRS, and BI will be determined at day 14. CT or MRI of the brain will be performed at day 7 ± 2 days for measurement of infarct volume [35,36] and lateral displacement of the pineal gland and septum pellucidum.

At three and six months, the mRS, BI, and NIHSS will be assessed. Serious adverse events and the number of days the patient was admitted on an IC unit, in the hospital, and/or rehabilitation centre or chronic nursing home will be recorded.

At one and three years, the mRS, BI, MADRS, VAS, and SF36 will be assessed by the research fellow or data manager. He/she will perform a standardised evaluation of each patient, including functional status, and will include the obtained information in an essay. Based on this essay, three members of the executive committee, who are blinded to treatment allocation, will determine the scores on the mRS and BI.

### Statistical aspects

In the primary analysis, outcome of all patients in the surgical group will be compared with that of all patients in the conservative treatment group. However, subgroup analyses will be performed based on the mode of conservative treatment (intensive care vs. stroke unit care), side of the lesion, and time of randomisation (within 48 hours versus between 48 and 96 hours). The sample size is based on the desire that in each of the two subgroups the superiority of surgical decompression over conservative treatment can be proved. All primary analyses will be performed on an intention-to-treat basis, but additional on-treatment analyses will also be performed. An interim analysis will be performed after the one-year follow-up of the first 30 patients.

Power calculations are hampered by the scarcity of data on clinical outcome in this patient group. In the non-randomised trial by Rieke et al., which is most comparable to the proposed study regarding patient group and treatment, 95% (20/21) of the patients in the IC treatment group had a poor outcome, compared with 50% (16/32) in the surgically treated group [24]. There are no data on outcome after 'standard' treatment, but this is not likely to be better than IC treatment. Based on an α of 0.05 and a β of 0.20, extrapolation of these data suggests that only 12 patients would have to be included in each group to demonstrate the superiority of surgical decompression over conservative treatment in a randomised trial. Assuming that 60% of the patients in the surgery group will have a poor outcome and 85% of the patients in each of the two conservative treatment subgroups, a group size of 28 patients would suffice to prove the superiority of decompressive surgery (table 1). Results of applying the same assumption to the complete treatment groups are shown in table 2.

**Table 1 T1:** Results expected for each of the two treatment arms assuming 60% poor outcome after surgery and 85% poor outcome after conservative treatment

	surgery n = 28	conservative treatment n = 28
Poor outcome (n)	17	24
RR (95% CI)	0.71 (0.51–0.99)	ref

RR denotes relative risk; CI, confidence interval. Conservative treatment indicates IC or SU treatment.

**Table 2 T2:** Results expected for the complete treatment groups assuming 60% poor outcome after surgery and 85% poor outcome after conservative treatment

	surgery n = 56	conservative treatment n = 56
Poor outcome (n)	34	48
RR (95% CI)	0.71 (0.56–0.90)	ref

RR denotes relative risk; CI, confidence interval.

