### Treatment allocation

After informed consent is obtained, patients will be randomised to either surgical or conservative treatment. Randomisation will be stratified for the intended mode of conservative treatment (intensive care or stroke unit care; see below). The choice of conservative treatment is left at the discretion of the local investigator, and will usually be the standard mode of treatment in the participating centre. Allocation to treatment will be made via a telephone call to a 24 hour randomisation service. Ideally, each treatment arm will consist of 56 patients. The total number of patients included in the trial will be 112.

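### 28 patients per group does not give the stated ability to prove superiority in each conservative-treatment stratum: power is about 57% per stratum and about 32% for both

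*Protocol article*

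**What the plan says.** All of this is in the protocol article, mostly under Statistical aspects.

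- The primary analysis is pooled: all surgical patients against all conservatively treated patients, by intention to treat.
- The sample size, however, is tied to a different aim, that "in each of the two subgroups the superiority of surgical decompression over conservative treatment can be proved". The surrounding text and the footnote to Table 1 show that the two subgroups are IC and SU care.
- The planning rates are the same in both strata: a poor outcome in 60% after surgery, against "85% of the patients in each of the two conservative treatment subgroups".
- From these rates the article concludes that "a group size of 28 patients would suffice to prove the superiority of decompressive surgery", and refers to Table 1 (17/28 versus 24/28 poor outcomes, RR 0.71, 95% CI 0.51–0.99). Table 2 gives the pooled counterpart (34/56 versus 48/56, RR 0.71, 0.56–0.90).
- Treatment allocation sets the total: "Ideally, each treatment arm will consist of 56 patients. The total number of patients included in the trial will be 112". Randomisation is stratified by intended mode of conservative treatment.
- It also states that "subgroup analyses will be performed based on the mode of conservative treatment (intensive care vs. stroke unit care), side of the lesion", and by time of randomisation.
- The phrase "Based on an α of 0.05 and a β of 0.20" introduces a separate calculation from a non-randomised study, which leads to 12 per group. It is not attached to the figure of 28.

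**The concern.** Table 1 shows what happens if the observed counts equal their expected values. That is not a power calculation. When the expected result lies just inside the significance boundary, chance variation puts the observed result outside it nearly half the time. A group size chosen this way cannot be said to suffice for proof.

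The plan asks for this in two strata at once. With the same true effect in both, and each stratum close to an even chance of significance, one success and one failure is the most likely result. A report that surgery beat SU care but not IC care, or the reverse, would look relevant to practice, because the article presents IC care as the experts' recommendation and SU care as the commonest Dutch practice. Under the plan's assumptions, such a split would reflect only low power.

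**Working it through.** **Inputs.** Poor outcome 60% (surgery) and 85% (conservative) in each stratum, 28 per arm per stratum, 56 per arm overall (Statistical aspects, Treatment allocation). Two-sided α of 0.05 is assumed: the article does not state sidedness, but its tables use 95% CIs. Equal strata are implied by Table 1 and not guaranteed.

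**1. The plan's own figures.** Expected counts are 0.60 × 28 = 16.8, rounded to 17, and 0.85 × 28 = 23.8, rounded to 24. RR = 17/24 = 0.708. SE(log RR) = √(1/17 − 1/28 + 1/24 − 1/28) = 0.1705. The 95% CI is exp(−0.3448 ± 1.96 × 0.1705) = 0.507 to 0.989, which reproduces Table 1. The same steps with 34/56 and 48/56 give 0.708 (0.559–0.897), which reproduces Table 2.

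Table 1 is on the edge. With 17 versus 24 the uncorrected chi-square gives p = 0.035 but Fisher's exact test gives p = 0.068. With 18 versus 24 the chi-square statistic is z = 1.85, no longer significant.

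**2. Power in one stratum.** With p̄ = 0.725:

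z = [0.25√28 − 1.96√(2 × 0.725 × 0.275)] / √(0.85 × 0.15 + 0.60 × 0.40) = (1.3229 − 1.2377) / 0.6062 = 0.141, so power = Φ(0.141) = 55.6%.

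Exact binomial enumeration gives 56.9% (uncorrected chi-square), 52.9% (RR confidence interval excluding 1) and 45.4% (Fisher).

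**3. Two strata.** Each stratum is randomised separately, so the two results are independent. With common power p, P(both significant) = p², P(exactly one) = 2p(1 − p), P(neither) = (1 − p)².

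| Test | p | Both | Exactly one | Neither |
|---|---|---|---|---|
| Chi-square, exact | 56.9% | 32.4% | 49.0% | 18.5% |
| RR CI, exact | 52.9% | 27.9% | 49.8% | 22.2% |
| Fisher, exact | 45.4% | 20.6% | 49.6% | 29.8% |
| Normal approximation | 55.6% | 30.9% | 49.4% | 19.7% |

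A simulation of 400,000 trials (chi-square) gave 49.1% for exactly one and 32.4% for both.

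**4. Sensitivity.** One-sided α of 0.05: power 68.0% per stratum, both 46.3%, exactly one 43.5%. Assumed unequal strata (normal approximation): 20 and 36 per arm give exactly one 52.6%, both 28.2%; 14 and 42 per arm give exactly one 59.0%, both 22.7%.

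**5. What 80% power would need.** The unpooled two-sided formula reproduces the article's 12 per group: 7.849 × (0.95 × 0.05 + 0.50 × 0.50) / 0.45² = 11.5. The same formula for 85% versus 60% gives 7.849 × 0.3675 / 0.25² = 46.2, hence 47. The pooled-variance version gives 49. At 49 per arm per stratum the total is 4 × 49 = 196, and exactly one stratum would still be significant in 2 × 0.8 × 0.2 = 32% of trials. For 80% power to succeed in both, each stratum needs √0.80 = 89.4% power: 64 per arm per stratum, 4 × 64 = 256 in total.

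**6. Pooled comparison.** With 56 per arm, z = (0.25√56 − 1.2377) / 0.6062 = 1.044, so power = 85.2% (exact chi-square 85.9%).

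**7. Interaction test on the risk difference.** SE = √2 × √(0.3675/28) = 0.162. Power for a 25-point effect in one stratum and none in the other is about Φ(0.25/0.162 − 1.96) = 34%. Under identical effects the test declares heterogeneity in about 5.8% of simulated trials.

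**The case against.** The quoted sentence is a sizing objective, not an analysis rule. The article nowhere says that strata will be compared by whether each reached significance, and a discordant pair is, strictly, a missed effect in one stratum. It becomes a false disagreement only if someone reads heterogeneity into it. Surgery versus IC care and surgery versus SU care are also legitimate separate questions, each with its own randomised comparison. And the pooled analysis is already primary. All of this stands, and it limits the point to the claim about 28 per group.

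Three stronger readings do not hold:

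- A reader might infer that the plan rejects an interaction test. It names none, but an analysis plan or full protocol that is not shown may contain one, so its absence here is no finding.
- A reader might count six within-subgroup comparisons (mode, side, time) and argue inflated false positives. The language of proof covers only the two mode strata; side and time are simply listed as subgroup analyses. For the two mode strata, the chance of at least one false positive favouring surgery is about 1 − 0.975² = 5%.
- A reader might say that the article claims 80% power for 28 per group. The β of 0.20 is attached to the 12-per-group calculation. What is claimed for 28 is that it suffices for proof, and that claim fails on its own terms.

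The low power per stratum is a sample-size problem that an interaction test does not cure. The test only guards against reading a chance split as a real difference.

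**Conclusion.** The point holds as a defect in the sample-size justification. Under the article's own rates, the design does not have the property on which its size is said to be based: the chance of proving superiority in both strata is about 32% (21–32% across the two-sided tests), and in a given stratum about 57% (45–57%). Exactly one stratum would be significant in about 49% of trials despite an identical true effect.

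These figures assume two-sided 0.05, 28 per arm in each stratum and the stated 60% and 85%. A one-sided test would raise the chance of success in both to 46%, still below one half. The unequal strata examined lower it further. The primary result is not affected, so this should be corrected but does not threaten the trial's main conclusion.

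**What to change.** - Withdraw the statement that 28 per group is enough to prove superiority in each subgroup, or restate it with its actual power: about 57% per stratum and about 32% for both.
- Justify N=112 by the pooled intention-to-treat comparison (about 85% power under 60% versus 85%), and name it as the only test that establishes superiority.
- For intended mode of conservative treatment as recorded at randomisation, and likewise for lesion side and time of randomisation, report the effect with a 95% CI in each level together with a treatment-by-subgroup interaction test.
- State that neither superiority nor lack of effect will be claimed from a single subgroup.

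No extra patients or data are needed. The cost is that the stand-alone subgroup claim is given up and the sample-size rationale has to be rewritten, since that claim is its present basis. The interaction test will be weak at 112 patients (about 34% power for a 25-point effect in one stratum and none in the other), so a non-significant interaction must not be read as showing equal effects.

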### Enrollment criteria

Patients can be enrolled in the study if they have 1. a diagnosis of acute ischaemic stroke in the territory of the middle cerebral artery, with an onset within 96 hours prior to the planned start of the trial treatment. Within this timeframe, it is advised to start treatment as soon as possible; 2. a score on the National Institutes of Health Stroke Scale (NIHSS) [29] ≥ 16 for right-sided lesions or ≥ 21 for left-sided lesions; 3. a gradual decrease in consciousness to a score of 13 or lower on the Glasgow Coma Scale (GCS) for right-sided lesions, or an eye and motor score of 9 or lower for left-sided lesions; 4. hypodensity on CT involving two thirds or more of the territory of the middle cerebral artery (MCA), and space-occupying oedema formation. (displacement of midline structures on CT is not a requirement for inclusion); and 5. age 18 up to and including 60 years. In addition, there must be a possibility to start trial treatment within 3 hours after randomisation, and written informed consent must be obtained from a representative of the patient.

Patients will be excluded from the study if they have 1. ischaemic stroke of the entire cerebral hemisphere (anterior, middle, and posterior cerebral artery territories); 2. a decrease in consciousness at least partially explained by a cause other than oedema formation, such as metabolic disturbances or medication; 3. two fixed dilated pupils; 4. been treated with a thrombolytic agent in the 12 hours preceding randomisation; 5. a known systemic bleeding disorder; 6. a pre-stroke score on the modified Rankin Scale (mRS) [30] of more than 1 or on the Barthel Index (BI) of less than 95 [31], 7. a life expectancy < 3 years, or 8. a serious illness that may confound treatment assessment.

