### Safety

In the conservative treatment group, patients will receive the standard care of the centre to which they have been admitted. For this reason, the components of the conservative treatment strategies will not be considered experimental, and need no detailed explanation in patient information letters.

Decompressive surgery consisting of a hemicraniectomy and a duraplasty may be complicated by the occurrence of local postoperative bleeding. In the two open, prospective studies of decompressive surgery for space-occupying hemispheric infarction, including a total of 63 patients, 3 patients (5%; 95% CI, 0 to 13) experienced an epidural haematoma, one (2%; 95% CI, 0 to 9) a subdural haematoma, and three (5%; 95% CI, 0 to 13) a space-occupying subarachnoid hygroma over the trepanation site. None of these complications led to an additional neurological deficit [9,25].

An adverse event is any unfavourable and unintended sign, symptom, or disease occurring during the follow-up period of the study. Adverse events occurring after randomisation will be recorded on the adverse event page of the CRF. A serious adverse event is defined as any adverse event that results in death, a life-threatening condition, inpatient hospitalisation or prolongation of existing hospitalisation, or persistent or significant disability/incapacity. An important medical event that may not result in one of the above conditions may be considered a serious adverse event when, based upon medical judgement, it may jeopardise the patient and may require medical or surgical intervention to prevent one of the outcomes above.

A reasonably-related adverse event is defined as one that is possibly, probably, or definitely related to the trial treatment. Adverse events that are serious and reasonably related to the trial treatment, and all deaths, require completion of the safety report, which should be faxed to the trial co-ordination centre within 5 working days of observation or notification of the event.

The Data Monitoring Committee performs analyses of the unblinded interim data and formulates recommendations for the Steering Committee on the continuation of the trial. The Data Monitoring Committee may also offer unsolicited recommendations.

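### The additional on-treatment analyses select patients on an event after randomisation, giving a bias of uncertain sign; a complier-average effect would be the better supportive analysis

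*Protocol article*

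**What the plan says.** Under Statistical aspects, the primary comparison is that "outcome of all patients in the surgical group will be compared with that of all patients in the conservative treatment group", and the analysis sets are settled in one sentence: "All primary analyses will be performed on an intention-to-treat basis, but additional on-treatment analyses will also be performed". The article says no more about the on-treatment analyses.

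Four other places bear on who could fail to receive the allocated treatment, and with what consequence:

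- Enrollment criteria: at entry "there must be a possibility to start trial treatment within 3 hours after randomisation", and patients with "two fixed dilated pupils" are excluded.
- Safety: "In the conservative treatment group, patients will receive the standard care of the centre to which they have been admitted".
- Outcome assessment: death counts as a poor outcome in the primary dichotomy at one year, and there is a secondary analysis "with case fatality as the measure of outcome".
- Treatment allocation: "Ideally, each treatment arm will consist of 56 patients".

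**The concern.** Whether a patient is operated on is decided after randomisation, and in this population it can depend on prognosis. Patients enter because their consciousness is falling. A surgical-arm patient who dies or herniates before theatre may never be operated on. Controls receive their centre's usual care, so they have no procedure to survive to before they count as treated.

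A per-protocol analysis would drop such a surgical-arm patient; an as-treated analysis would count the patient as conservatively treated. Either way a near-certain poor outcome leaves the surgical arm, and the groups compared are no longer those that randomisation made.

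Other departures select in the opposite direction. The result would mix these selections and would not estimate the effect of receiving surgery. With 56 patients per arm, a handful of departures can matter. At stake is the reading of a secondary result for the primary outcome and for case fatality, not the trial's main test.

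**Working it through.** **Inputs.** From the article: 56 patients per arm (Treatment allocation); poor outcome assumed in 60% after surgery and 85% after conservative treatment, and α 0.05 (Statistical aspects). The article does not state whether α is one- or two-sided; I take it as two-sided, so 2.5% in the direction of surgery. Assumed, because the article gives no figure: the number *m* of surgical-arm patients not operated on, and that all of them have a poor outcome.

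**1. The plan's own figure.** Table 2 expects 34/56 against 48/56 poor outcomes. RR = 34/48 = 0.708. SE of log RR = √(1/34 − 1/56 + 1/48 − 1/56) = 0.1205. The 95% CI is 0.708 × exp(±1.96 × 0.1205) = 0.559 to 0.897, which matches the stated 0.71 (0.56–0.90). This describes the complete randomised groups. There is no corresponding figure for an on-treatment analysis.

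**2. Apparent effect when there is none.** Let the poor-outcome probability be *p* in both arms.

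- Surgical group after removal: (56p − m)/(56 − m).
- Comparator, per-protocol: p. Comparator, as-treated: (56p + m)/(56 + m).

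For m = 3 and p = 0.85 (56p = 47.6), the surgical proportion is 44.6/53 = 0.8415. Per-protocol RR = 0.8415/0.85 = 0.990. As-treated, the comparator is 50.6/59 = 0.8576 and RR = 0.981.

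For m = 3 and p = 0.60 (56p = 33.6), the surgical proportion is 30.6/53 = 0.5774. Per-protocol RR = 0.962. As-treated, the comparator is 36.6/59 = 0.6203 and RR = 0.931.

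**3. Chance of falsely finding surgery superior.** Exact binomial enumeration, pooled z test, z > 1.96, fixed m:

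| Event rate, both arms | m of 56 | Per-protocol: RR, error | As-treated: RR, error |
|---|---|---|---|
| 85% | 0 | 1.00, 2.5% | 1.00, 2.5% |
| 85% | 3 | 0.990, 3.4% | 0.981, 4.3% |
| 85% | 5 | 0.983, 4.0% | 0.969, 6.3% |
| 60% | 0 | 1.00, 2.4% | 1.00, 2.4% |
| 60% | 3 | 0.962, 4.9% | 0.931, 7.2% |
| 60% | 5 | 0.935, 7.0% | 0.886, 11.4% |

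If the number not operated on is random rather than fixed, with mean 3 of 56, simulation gives 3.4% and 4.4% at the 85% rate, and 4.4% and 6.9% at 60%. With 10% not operated on, simulation gives about 4.3% (per-protocol) and 6.8% (as-treated) at 85%, 5.7% and 10.5% at 70%, and 6.9% and 13.9% at 60%. Intention-to-treat stays at about 2.5% throughout.

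**4. Departures that work the other way.** Again no true effect and p = 0.85.

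- Three controls deteriorate, are operated on and have a poor outcome. As-treated: 50.6/59 against 44.6/53, RR 1.02. Per-protocol: 47.6/56 against 44.6/53, RR 1.01.
- Three surgical patients are not operated on because they improve, and have a good outcome. Per-protocol: 47.6/53 = 0.898 against 0.85, RR 1.06.
- Three preoperative surgical deaths together with three such control crossovers: 47.6/56 in both groups (as-treated) or 44.6/53 in both (per-protocol), RR 1.00.

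**5. The alternative on the same data.** Complier-average risk difference = intention-to-treat risk difference ÷ (proportion operated on in the surgical arm − proportion operated on in the control arm). With no effect the numerator has expectation zero whatever the departures. With Table 2's figures the numerator is (34 − 48)/56 = −0.25. If 3 of 56 surgical patients are not operated on and no control is, the estimate is −0.25/(53/56) = −0.264. If 3 controls are also operated on, it is −0.25/(50/56) = −0.28.

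**The case against.** The strongest case against is that no faulty method is written down. The article names on-treatment analyses without saying who is dropped, moved or censored, and a condensed article may leave that to the full protocol or analysis plan. This stands to the extent that the missing definition is not itself a finding. It does not remove the point, because the analyses are a stated commitment and both usual forms share the weakness.

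A reader might go further and infer that these analyses will remove early deaths from the surgical arm only and so manufacture a benefit of surgery. The documents do not support that:

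- The direction depends on why treatment was not received, and step 4 shows realistic departures that cancel or reverse the bias.
- The entry requirement on timing covers trial treatment in general, and intensive care has a recommended minimum duration, so controls can depart from assigned care too.
- Being able to start within 3 hours, with the pupil exclusion, should keep preoperative losses few.
- No figure in the article supports 10% or more not operated on. The 60% event rate lies below the article's own conservative-treatment figures (85% poor outcome, about 80% case fatality), so the larger error rates are the upper end of the illustration.

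It is also fair that an additional on-treatment analysis beside a primary intention-to-treat analysis is conventional, and that the word additional already signals lower standing. Finally, a complier-average effect needs assumptions of its own: assignment acts on outcome only through surgery, and no patient would be operated on only if assigned to control. These must be stated; in an open trial the first is not automatic.

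**Conclusion.** The point holds as a secondary one. Either usual on-treatment analysis breaks the randomised comparison by selecting on a prognosis-related event, and the resulting bias is of uncertain sign. The primary analysis and its conclusion are untouched.

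Where preoperative deaths or herniation dominate, the bias favours surgery. At the article's 85% rate and 3 of 56 not operated on, it is small: RR 0.98–0.99. It grows with more non-operation and with a lower event rate, which matters most for case fatality if that proves lower than expected. These sizes rest on an assumed non-operation rate, on every such patient having a poor outcome, and on no control being operated on. The article gives no data on any of the three.

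**What to change.** In Statistical aspects, replace the on-treatment analyses with one supportive treatment-received analysis: a complier-average effect with the randomised arm as instrument, stratified by intended mode of conservative treatment. Estimate it as the intention-to-treat risk difference divided by the between-arm difference in the proportion operated on.

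- Keep every randomised patient in the assigned arm.
- State the exclusion-restriction and monotonicity assumptions.
- Report, by arm and with reasons, how many surgical patients were not operated on and how many controls were operated on later.
- If a conventional on-treatment result is still shown, define it and present it as descriptive only, without a claim of superiority.

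The cost is a change of wording and minor analysis work. The data (operated on or not, when and why) are largely what an on-treatment analysis needs anyway. The downside is a slightly wider interval. Sample size, primary analysis and patient care do not change.

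### 28 patients per group do not suffice within each conservative-treatment subgroup: power at 60% vs 85% is about 45–57%, and about 21–32% for success in both

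*Protocol article*

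**What the plan says.** All of this is in the protocol article, mostly under Statistical aspects.

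- Purpose of the sample size, which is proof at subgroup level: "The sample size is based on the desire that in each of the two subgroups the superiority of surgical decompression over conservative treatment". The subgroups are those defined by mode of conservative treatment, which is also the stratification factor for randomisation.
- Error rates: "Based on an α of 0.05 and a β of 0.20" is the only specification given. In the text it introduces the figure of 12 per group, which is derived from a non-randomised study: "95% (20/21) of the patients in the IC treatment group had a poor outcome, compared with 50% (16/32) in the surgically treated group".
- The article then moves to more cautious rates, the same for both subgroups ("Assuming that 60% of the patients in the surgery group will have a poor outcome and 85% of the patients in each of the two"), and concludes that "a group size of 28 patients would suffice to prove the superiority of decompressive surgery", citing Table 1.
- Table 1 lists 17/28 vs 24/28 poor outcomes, relative risk 0.71 (95% CI 0.51 to 0.99). Table 2 does the same for the whole trial: 34/56 vs 48/56, relative risk 0.71 (0.56 to 0.90).
- Treatment allocation sets the total at 112, ideally 56 per arm, and says of the stratum variable: "The choice of conservative treatment is left at the discretion of the local investigator".

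**The concern.** Two subgroups with two arms of 28 make 112, so the subgroup claim is the stated reason for the size of the trial. Table 1, however, is not a power calculation. It shows what the confidence interval would be if the observed counts came out exactly as expected, and the upper limit is then 0.99. When the expected result sits on the edge of significance, about half of all replications fall on the wrong side of that edge.

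If so, the design lacks the property on which its size is said to rest. The risk lies in interpretation: a reader told that 28 per group is enough could take a non-significant intensive care or stroke unit stratum as evidence that surgery does not help there. Under the article's own assumptions, that result is about as likely as not.

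**Working it through.** **Inputs** (Statistical aspects unless noted): poor outcome 60% with surgery and 85% with conservative treatment; 28 per arm per subgroup; 56 per arm overall (also Treatment allocation); α 0.05, β 0.20. Sidedness is not stated. I take α as two-sided because both tables use 95% intervals, and give one-sided results below.

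**1. Reproduce the article's own figures.**

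*Tables.* SE of log RR = √(1/a − 1/n + 1/b − 1/n).
- Table 1: √(1/17 − 1/28 + 1/24 − 1/28) = 0.1705. RR = 17/24 = 0.708, 95% CI 0.507 to 0.989.
- Table 2: √(1/34 − 1/56 + 1/48 − 1/56) = 0.1205. RR = 0.708, 95% CI 0.559 to 0.897.

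Both match.

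*12 per group.* Unpooled formula: n = (1.960 + 0.842)² × [p₁(1−p₁) + p₂(1−p₂)] / (p₁−p₂)², with (1.960 + 0.842)² = 7.849.
- 50% vs 95%: 7.849 × (0.25 + 0.0475) / 0.45² = 11.5, so 12. This matches.

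**2. Apply the same formula to 60% vs 85%.**
- 7.849 × (0.24 + 0.1275) / 0.25² = 46.2, so **47 per group**, not 28.

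Other variants at 80% power:

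| Variant | Two-sided | One-sided |
|---|---|---|
| Unpooled | 47 | 37 |
| Arcsine | 48 | 38 |
| Pooled | 49 | 39 |
| Pooled, continuity-corrected | 57 | 47 |

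None gives 28.

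**3. Power actually available.** Approximate check on the article's own scale: log(0.85/0.60) = 0.348; SE at n = 28 is √(0.40/(28 × 0.60) + 0.15/(28 × 0.85)) = 0.1735; ratio 2.007; power ≈ Φ(2.007 − 1.960) = 52%.

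Exact enumeration of the two binomial distributions, two-sided 0.05:

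| Criterion | 28 vs 28 | Both subgroups (squared) | 56 vs 56 |
|---|---|---|---|
| RR 95% CI excludes 1 | 52.9% | 27.9% | 84.8% |
| Pearson chi-square | 56.9% | 32.4% | 85.9% |
| Fisher exact | 45.4% | 20.6% | 80.8% |

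Squaring is valid because the two strata contain different patients. A one-sided test at 0.05 would still give only 57% (Fisher) to 70% (Pearson) per subgroup.

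**4. How fragile Table 1 is.** One patient moves the upper limit past 1: 18/28 vs 24/28 gives 1.03, and 17/28 vs 23/28 gives 1.04. Table 1's own counts give p = 0.035 uncorrected and p = 0.068 by Fisher's test.

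**5. Stratum sizes.** Steps 2 and 3 assume an even split of 56 patients per stratum. Nothing in the article fixes this, since the mode is chosen locally and only the total is set. As an illustration only (the article gives no proportions), a 70:30 split gives about 39 and 17 per arm, with Pearson power of 72% and 36%.

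**The case against.** The strongest points on the other side are these.

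- *β 0.20 belongs to the 12-per-group sentence.* Literally, yes; applying it to 28 is an inference. But it is the only error target given, it stands in the same paragraph on power, and the next step changes only the assumed rates. Even with no β at all, a size that misses significance in 43–55% of trials when its assumptions are true cannot be called sufficient.
- *The article shows its criterion openly, and the tables are correct.* Both statements are true. The fault is that the criterion does not support the conclusion drawn from it.
- *Fisher's test is not named in the article.* Also true, so the low ends (45% and 21%) depend on a conservative test. On the article's own relative-risk scale the figures are 53% and 28%, which leaves the conclusion unchanged.
- *At the observed rates of 50% vs 95%, 28 per arm would have 97–99% power.* This is correct by exact calculation, but the article sets those rates aside and makes its claim for 60% vs 85%.
- *All 56 surgical patients could serve as comparator for each subgroup.* Table 1 uses 28 vs 28, and 56 vs 28 would still give only 64–74%.
- *The primary analysis is unaffected.* This stands in full and limits the scope of the point.
- *No decision rule says that a non-significant stratum means failure.* This also stands; misreading is a risk, not something the article prescribes.

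**Conclusion.** The claim is wrong as written. For 60% vs 85% and two-sided α 0.05, 28 per arm gives about 45–57% power in a subgroup, a type II error of 0.43–0.55 against the only stated target of 0.20. Success in both subgroups, which is the declared aim, has a probability of about 21–32%. Reaching 80% power in one subgroup needs 47–49 per arm (57 with continuity correction), or 188–196 patients over two subgroups (4 × 47 to 4 × 49). These figures rest on the article's planning rates, no loss to follow-up, and an even split between the two modes of care; an uneven split lowers power in the smaller stratum.

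The defect is confined to the subgroup aim and the stated basis of the sample size. The 112 patients do support the overall comparison, with 81–86% power under the same assumptions. It still has to be corrected, because the published rationale for the trial's size is a property the design does not have.

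**What to change.** Keep 112 patients and reword Statistical aspects:

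1. State that the trial is sized for the comparison of all surgical with all conservatively treated patients: 56 per arm, 60% vs 85% poor outcome, two-sided α 0.05, power 81–86% depending on the test.
2. Delete the claim that 28 per group is sufficient, and the sentence that bases the sample size on each subgroup.
3. State that a stratum reaching 28 per arm has about 45–57% power (about 21–32% for both), and that stratum sizes follow local choice of conservative treatment and are not guaranteed.
4. State that stratum results are supportive, and that a non-significant stratum is not evidence of no benefit.
5. Label Table 1 as expected precision, not as justification of power.

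The cost is rewording. No patients are added and no analysis changes; the price is a less favourable subgroup statement.
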